**Fig. 1 Fig1:**
[figure not shown]
Allocation of the two interventions in four strata across 45 communities

The study is registered at the National Institute for Health’s ClinicalTrials.gov. Enrolment started in February 2018 and follow up will be completed in December 2021.

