#### Exclusion criteria

Individuals are not eligible to receive any of the HITS interventions if they have refused to participate in the AHRI HIV surveillance or report to be already on ART. Individuals mentally or physically challenged to provide consent are also excluded.

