### Outcomes

The goal of the trial is to establish whether the provision of micro-incentives and a male-targeted HIV-specific decision-support app will increase uptake of HIV testing and linkage to HIV care thus, ultimately reducing HIV-related mortality in men and population-level HIV incidence in young women. The trial’s primary endpoints are to measure the impact of the interventions at both individual and population-levels as follows:HIV testing uptake at point of test offer in menHIV treatment linkage in men at 1-yearPopulation-level HIV viral suppression in men after 1-yearPopulation-level HIV-related mortality in men after 3-yearsPopulation-level HIV incidence in young women (15–30 years of age) after 3-years

Specifically, the study compares differences in the percentage that received the rapid HIV test at home among those offered the test in men among the intervention arms compared to the SoC arm. The study will also compare the percentage who visited study clinics and initiated ART in men at 1-year after the home-based HIV-positive test, as well as prevalence of detectable viremia (detection limit of > 1550 copies/ml) obtained from the DBS in men. Changes in the number of HIV-related deaths and mortality rates in men and changes in the number of new HIV infections and HIV incidence rates in young women 3 years after the home-based HIV test will be compared across the arms. Secondary outcomes that will be measured in the study are shown in Table 1.

**Table 1 Tab1:** Secondary outcomes of the study

No	Secondary outcome	Description	Time frame
1	HIV testing uptake at point of test offer in women	% received rapid HIV test at home among those offered the test in women	Baseline
2	HIV treatment linkage at 1 year in women	% who visited the Department of Health clinics in the study area and initiated ART in women	Year 1
3	Population-level HIV viral suppression (both sexes)	Change in proportion with detectable viremia in both men and women; HIV testing and viral load measurements are performed on the DBS samples collected during the annual individual survey	Year 1
4	Population-level HIV viral suppression (both sexes)	Change in proportion with detectable viremia in both men and women; HIV testing and viral load measurements are performed on the DBS samples collected during the annual individual survey	Year 3

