18	Diabetes Healthcare utilization in men and women	% reported starting diabetes treatment in the past 12 months	Year 1
19	Hypertension healthcare utilization in men and women	% reported starting blood pressure treatment in the past 12 months in men and women	Year 1
20	Household wealth (household assets)	Number of household assets (selected from a predefined list of 32 assets)	Year 3
21	Household wealth (food security)	% of adults in the household ever cutting the size of meals or missing meals due to insufficient money for food in the past 12 months	Year 3
22	Partnership patterns in men and women	% reporting having more than one sexual partner in the past 12 months in men and women	Year 1
23	Retention in HIV care in men and women	% who are retained in care (% patients having an ART clinic visit in previous 3 months) at 1-year post-initiation in men and women	Year 1
24	Retention in HIV care in men and women	% who are retained in care (% patients having an ART clinic visit in previous 3 months) at 3 years post-initiation in men and women	Year 3
25	Patient viral suppression in men and women	% who are remain virally suppressed (% patients where virus is undetectable) 1-year post-initiation in men and women	Year 1
26	Patient viral suppression in men and women	% who are remain virally suppressed (% patients where virus is undetectable) 3-years post-initiation in men and women	Year 3

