### Trial status

The study is ongoing.  Intervention delivery started in February 2018 and ended in December 2018. Participant follow-up will continue until the end of 2021. No articles containing the results of this study have been published or submitted for publication.

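### Secondary outcomes 24 and 26 are set at 3 years after ART initiation, a time point that only people starting ART by 31 December 2018 can reach within the stated follow-up

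*Protocol article*

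**What the plan says.** In the Outcomes section, Table 1, outcome 24 is the percentage retained in care, defined by a recent ART clinic visit, "at 3 years post-initiation in men and women". Outcome 26 is the percentage virally suppressed at the same distance from initiation. Both carry the time frame Year 3.

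Three other statements fix the calendar:

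- Trial status gives the testing window and the end of observation: "Intervention delivery started in February 2018 and ended in December 2018. Participant follow-up will continue until the end of 2021". The Study design section agrees: "Enrolment started in February 2018 and follow up will be completed in December 2021".
- The Outcomes text counts treatment linkage as those who "initiated ART in men at 1-year after the home-based HIV-positive test". Table 1 gives the matching outcome in women a Year 1 time frame.
- The Exclusion criteria bar from the interventions those who "report to be already on ART". The initiations that the interventions can influence therefore follow the 2018 home test.

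The 3-year mortality and incidence endpoints are timed differently. The Outcomes text counts their 3 years from the home-based test.

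**The concern.** The article fixes the clock (ART initiation), the horizon (3 years) and the end of follow-up (December 2021), and these do not fit together for everyone whose initiation is counted. Those who start ART in 2019 cannot contribute a 3-year status.

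The loss is not random. Whether a person is assessable depends on test date plus delay to ART, and the delay is something the interventions are meant to shorten. The second voucher requires presentation within 6 weeks, and EPIC-HIV 2 goes to men not linked within a month. Outcomes 24 and 26 already condition on initiating ART, which happens after randomisation. Truncation at the end of 2021 adds a second selection. If that selection is uneven between arms, a difference in the 3-year percentages could reflect who is assessable and not who stays in care or suppressed.

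**Working it through.** **Calendar.** Inputs are from Trial status, Study design and Outcomes.

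- Latest start with 3 full years observed: 31 Dec 2021 − 3 years = 31 Dec 2018.
- Latest counted start: last test (Dec 2018) + 1 year = Dec 2019.
- Time after initiation for that person: Dec 2021 − Dec 2019 = about 2.0 years.
- Follow-up needed for 3 years in all counted initiators: Dec 2019 + 3 years = Dec 2022.
- Three years from the home test: Dec 2018 + 3 years = Dec 2021, which just fits.
- One year after initiation (outcomes 23 and 25): Dec 2019 + 1 year = Dec 2020, which fits.

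**How many are lost.** The documents give no delay distribution, so this part is illustrative. Assumptions:

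- Test dates are uniform from 1 Feb to 31 Dec 2018, so W = 333 days.
- Delay D from test to ART is exponential, truncated at L = 365 days, with λ = ln 2 / m. Here m is the median before truncation. As an extreme, D is uniform over the year.

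A person is observable if test date + D falls by 31 Dec 2018. The observable share is

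[1 − (1 − e^(−λW)) / (λW)] / (1 − e^(−λL)), or W / (2L) for uniform delay.

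- m = 30: λW = 7.694, so (1 − 0.130) / 0.9998 = 0.87.
- m = 60: λW = 3.847, so (1 − 0.254) / 0.985 = 0.76.
- Uniform: 333 / 730 = 0.46.

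| Assumed delay | Observable | Unobservable | Observable if linked within 6 weeks | Observable if linked later |
|---|---|---|---|---|
| m = 15 days | 94% | 6% | 96% | 81% |
| m = 30 days | 87% | 13% | 95% | 74% |
| m = 60 days | 76% | 24% | 94% | 64% |
| m = 90 days | 68% | 32% | 94% | 57% |
| m = 180 days | 58% | 42% | 94% | 49% |
| Uniform over 1 year | 46% | 54% | 94% | 39% |

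In every row the fast linkers are kept more often than the slow ones. With m = 60, for example, people linking after 6 weeks are 61% of all initiators but 51% of those assessable.

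**Between arms.** With the same delay distribution and the same visit calendar, the excluded shares are equal. If m were 30 days in an intervention arm and 60 days in standard of care (assumed), 13% against 24% would be excluded. Visit dates could also differ by arm: week blocks are visited in sequence, and the Randomisation section stratifies on HIV incidence, not on visit date.

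**The case against.** The strongest reply is that handling of incomplete follow-up belongs in an analysis plan that is not shown. Table 1 does not say that every 1-year initiator enters the denominator, and routine clinic records could be read after 2021. That is fair as far as it goes. But the article itself fixes the clock, the horizon and the end of follow-up, and it mentions no later extraction. An analysis plan could restrict or censor; it could not make the stated time point reachable for 2019 initiators.

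Three stronger readings are tempting, and the documents do not support them.

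- **A large contrast by arm.** A reader might set about 7% lost in the voucher arms against 25% to 54% in standard of care. The 7% (1.5 / (2 × 11), in months) needs every voucher-arm initiator to link within 6 weeks. Yet EPIC-HIV 2 is planned in the combined arm for men unlinked at a month, and linkage is counted to 1 year in all arms. The 25% (exponential delay, mean 3 months) and the 54% (delay even over 12 months) are equally assumed, although positives are referred for care within 10 days. No passage gives delays by arm.
- **Only fast linkers remain.** The cut is on the calendar date of initiation. A person tested on 1 February 2018 can take up to 333 days and still be observed, while one tested in late December is lost even after a short delay. It is a tilt, partly by visit date. That slow linkers are retained less well is plausible, but the article does not say so.
- **The 1-year versions share the fault.** They do not; the latest time point falls in December 2020.

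It is also true that two of 26 secondary outcomes are affected, and no primary endpoint or power figure.

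**Conclusion.** The concern holds in limited form. That outcomes 24 and 26 cannot be measured as defined for those starting ART after 31 December 2018 is certain from the article's own dates. The size is not: 6% to 54% rests on assumed delays and uniform test dates. Selection towards early testers and fast linkers follows from the cut-off. A difference between arms is conditional on an intervention effect on linkage speed or on unequal visit dates, and 13% against 24% only illustrates it. The definitions should be changed, at the weight of a secondary-outcome correction.

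**What to change.** Reword outcomes 24 and 26 only, in one of two ways.

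1. **Clock from the positive home test.** Report the percentage in care, and the percentage suppressed, 3 years after that test, counting those who never initiate as not retained and not suppressed. This matches the trial's other 3-year endpoints and fits December 2021. State plainly that it turns a measure among ART patients into a test-to-care measure, and that it still conditions on testing at home, which is itself post-randomisation and a target of the first voucher and EPIC-HIV 1.
2. **Clock from initiation, at 24 months.** Every counted initiator can reach this by December 2021, though the last have no slack. Assess status at that time point; both outcomes are statuses, so a time-to-event estimate is not a natural fit. The comparison still conditions on having initiated, and the 3-year horizon is given up.

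Whichever is chosen, label any figure at 3 years post-initiation as descriptive and limited to people starting ART by December 2018. Outcomes 23 and 25 need no change on this ground.

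The cost is the rewording of two secondary outcomes. The clinic records are already collected through TIER.net. Under the first option the percentages will be lower, because non-initiators count.

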### Data collection and measures

Participants are enrolled into the HITS trial during the ongoing annual individual HIV surveillance and routinely followed up between 2018 and 2021 (BREC Ref: BE290/16).

Trained fieldworkers visit participants at home once a year to conduct household and individual surveys using tablet-based computers. Data on demographic information, general health, and sexual behaviour (including contraceptive use, sexual activity and pregnancy history) are collected via the REDCap database [27]. Participating individuals are offered rapid HIV testing. Consenting individuals undergo confidential HIV pre- and post-test counselling according to the Department of Health procedures. A rapid HIV test is performed and test results are provided approximately 20 min after the testing. Participants who consent to the HIV surveillance have blood collected on a filter paper as DBS, which are stored at the AHRI Biorepository in Durban [28]. A 4th generation HIV ELISA (Genscreen™ ULTRA HIV Ag-Ab (Biorad, Marnes-la-Coquette, France) adopted and evaluated in-house by the AHRI Diagnostic Research Laboratory (unpublished data) is used for testing of all DBS samples. All HIV ELISA positive DBS samples are subjected to HIV viral load determination using the automated Nuclisens EasyMag® (Biomerieux, Marcy-l’Etiole, France). Viral load testing is performed on the same day as the extraction.

Individuals who test positive for HIV are referred to the nearby Department of Health clinics to receive HIV care within 10 days of the HIV test date. Data on linkage to care is collected from the Department of Health through TIER.net (i.e. an electronic patient records management system that contains information on all clinic visits for people on ART, including data for all patients attending the 17 clinics in the Hlabisa health sub-district and the Hlabisa hospital) and clinic attendance data (where date and reason for attendance are collected for all consenting individuals in the programme area who attend one of the 11 clinics serving the programme area). All deaths are ascertained by verbal autopsies with closest care givers using a questionnaire based on the INDEPTH/World Health Organization (WHO) standard questionnaire [29].

Data is collected and managed by AHRI Research Data management within the routine AHRI HIV and demographic surveillance study databases as per AHRI comprehensive study procedures. The database has strictly restricted access via a data enclave on a secure server.

### Randomisation and blinding

Randomisation was performed by the trial statistician prior to intervention rollout to ensure that each arm has similar baseline HIV incidence rates among women aged 15 and 30 years. First, all 45 clusters were stratified by HIV incidence in young women using data from 7605 young women aged 15 and 30 years old, who were residents in the PIPSA between 2006 and 2015 at least for 1 year. A total of 34551 person years and 1636 seroconversion events have been recorded, yielding overall 4.7 new infections per 100 person years. Then the 45 clusters were divided into four strata according to their HIV incidence rate such that stratum 1 comprises clusters with the lowest incidence rate, while stratum 4 comprises clusters with the highest incidence rate. Each of Arm 1, 2, and 3 consists of two clusters from each of the four incidence stratum (thus a total of eight clusters per arm). Arm 4 (SoC) consists of five clusters from each of the incidence stratum 1, 2, and 4, and six clusters from incidence stratum 3 (thus a total of 25-clusters). The study is an open label trial.

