#### Statistical analysis

All primary analyses (both primary and secondary endpoints) will be intent-to-treat (ITT). For the binary primary outcomes – HIV testing uptake and HIV treatment linkage – we will use generalized linear models with Poisson distribution, log link function, and robust error terms to determine effect sizes (risk ratios). We will fit beta regression models for incidence and mortality rates [30, 31]. We will also adjust for both baseline endpoints and clustering through random effects. Under the difference-in-differences study design, the individuals are followed in two periods of time: the “before” and the “after” period, where the interventions occur in the “after” period [32]. The goal of the statistical analysis is to estimate the average treatment effect for the treated clusters (week blocks). We will make the usual assumption of parallel trend, that is, on average, the outcomes for all the clusters in the four arms would have followed a parallel path over time in the absence of the intervention [33]. Our generalized linear models will include fixed effects for the “before” and the “after” time periods, the grouping of the clusters in four arms, and the interaction between time periods and arms.

For the two survival-analytic primary endpoints – population-level mortality among men and population-level HIV incidence among women – we will use the Cox proportional hazards model to determine effect sizes (hazard ratios). If the proportional hazards assumption of the Cox model is violated, we will use appropriate alternative survival analytic models. We will use data from the period 2004–2017 for baseline endpoint adjustment. In addition, to the ITT analyses, we will measure intervention effects adjusted for non-compliance using instrumental variable (IV) approaches.

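### The listed models omit the four-level incidence stratum used to randomise clusters; the effect is conservative and probably modest, and matters most for men's home-test uptake and linkage

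*Protocol article*

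**What the plan says.** **Allocation** (protocol article, Randomisation and blinding). "First, all 45 clusters were stratified by HIV incidence in young women". "Then the 45 clusters were divided into four strata according to their HIV incidence rate". "Each of Arm 1, 2, and 3 consists of two clusters from each of the four incidence stratum". "Arm 4 (SoC) consists of five clusters from each of the incidence stratum 1, 2, and 4, and six clusters from incidence stratum 3". These counts give 21 standard-of-care clusters, as in the abstract and the power section. The same paragraph then prints a total of 25, which conflicts with its own sum; 21 is used here.

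**Analysis** (Statistical analysis). The generalised linear models carry fixed effects for the two time periods, "the grouping of the clusters in four arms, and the interaction between time periods and arms". The section also adjusts for the baseline value of the endpoint, and for clustering through random effects. Mortality in men and incidence in women are assigned to Cox models, with 2004–2017 data for the baseline adjustment. The incidence stratum is not named for any model.

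**Before data** (Study setting). Home-based rapid testing joined the annual surveillance in 2017. Intervention delivery began in February 2018 (Trial status).

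**The concern.** Allocating within strata takes between-stratum variation out of the arm contrast. If the analysis leaves that variation in the residual, the reported standard error exceeds the real sampling variability of the estimate. Tests then run below their nominal size, and some of the precision gained by stratifying is not used. With eight clusters in each intervention arm, even a modest loss is unwelcome.

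The baseline-endpoint adjustment can stand in for the stratum only where the baseline endpoint is the variable from which the strata were cut. That holds for HIV incidence in young women. For the other four primary endpoints (test uptake, linkage, viral suppression and mortality in men) the baseline endpoint is a different variable. For uptake and linkage it may hardly exist.

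**Working it through.** **Inputs from the article**

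- Strata: 3 × 2 + 5 = 11, 11, 3 × 2 + 6 = 12, and 11, which sum to 45.
- Baseline incidence: 1636 / 34551 = 4.74 per 100 person-years, which reproduces the stated 4.7.
- Three years of follow-up per cluster, at the baseline rate of accrual: 34551 / 10 / 45 × 3 = 230.3 person-years, and 230.3 × 0.0474 = 10.9 events.

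**Assumed.** The article gives no between-cluster coefficient of variation (k). Values of 0.15, 0.25 and 0.4 were used, with or without extra cluster-by-period variation of 0.1. How much of the variance in men's outcomes the stratum explains is not given either.

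**Step 1: the listed difference-in-differences model.** The effect is period by arm. A stratum effect that is constant over time adds equally to both periods of a cluster and drops out. In 60 simulated trials with this allocation (k = 0.25, cluster-by-period variation 0.1), adding a stratum main effect changed the estimate by less than 1e-14. The ratio of standard errors, without to with stratum, was 1.000 in an exchangeable Poisson GEE and averaged 1.005 in a linear mixed model on log rates.

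**Step 2: stratum by period.** In change-score form, a stratum term is the equivalent of stratum by period. Mean standard error and rejection rate under the null, for incidence:

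| k | Cluster-by-period | SE without | SE with | Cut | Rejection without / with |
|---|---|---|---|---|---|
| 0.15 | 0 | 0.1481 | 0.1395 | 5.8% | 3.4% / 5.0% |
| 0.25 | 0 | 0.1503 | 0.1450 | 3.5% | 4.2% / 4.8% |
| 0.25 | 0.1 | 0.1573 | 0.1524 | 3.1% | 3.7% / 3.9% |
| 0.4 | 0.1 | 0.1632 | 0.1603 | 1.8% | 4.5% / 4.5% |

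The cut is about 2–6%, and rejection stays at or below 5%. In this simulation the strata were cut from the same baseline counts that enter the change score, so the range does not transfer directly to men's outcomes.

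**Step 3: incidence adjusted for its own baseline.** Adding stratum does not lower the standard error: 0.1442 becomes 0.1457 at k = 0.25, a ratio of 0.1457 / 0.1442 = 1.01. The continuous baseline rate already holds what the stratum holds.

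**Step 4: a single-period model with no before value.** If the stratum explains a share R² of between-cluster variance, leaving it out inflates the standard error by at most 1/√(1 − R²):

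- R² = 0.05: 1/√0.95 = 1.026, about 3%.
- R² = 0.25: 1/√0.75 = 1.155, about 15%.

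These are upper bounds, because within-cluster sampling variance is ignored. If only a share w of the variance of a cluster's result is between-cluster, the factor is 1/√(1 − wR²). With w = 0.5 as an illustration, R² = 0.05 gives 1/√0.975 = 1.013 and R² = 0.25 gives 1/√0.875 = 1.069.

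**The case against.** The case against is substantial, and most of it stands.

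- **The planned contrast largely protects itself.** Differencing removes any time-constant stratum effect, and for incidence in young women the baseline adjustment uses a finer version of the stratifying variable. Steps 1 and 3 confirm both.
- **Nothing shows that the strata predict men's outcomes.** They were cut on women's incidence. An outcome's own baseline, where it exists, is normally the more direct adjuster. This stands, and it is why Step 4 gives a range and not an estimate.
- **The list of terms may not be closed.** Baseline values and random effects are added separately, and a statistical analysis plan that is not shown may add the stratum. This too stands. But the article does set out its model terms, and the one design variable used to restrict allocation is not among them.

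Two stronger readings are tempting and are not supported.

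- **A large loss of precision.** A reader might infer this from a comparison of arms on follow-up incidence alone: at k = 0.25 the standard error is then 0.1673 without stratum against 0.1472 with it, and the type I error is 2.9% against 5.1%. The article does not plan that model. It also concerns the endpoint that baseline adjustment already covers.
- **An avoidable imbalance.** Standard of care takes "six clusters from incidence stratum 3", so 6/21 = 28.6% of its clusters come from that stratum, against 2/8 = 25% in each intervention arm. But 45 = 4 × 11 + 1, so with two clusters per stratum in each intervention arm, one stratum must supply a sixth control cluster. Across several assumed sets of stratum rates, mean baseline incidence under standard of care is only 0.3–1.1% higher, against a target reduction of 25%.

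**Conclusion.** The point holds as a minor gap in specification. The stratum used to restrict allocation is absent from the stated models, and the consequence is standard errors that are somewhat too large. It does not inflate false positives or cause material bias.

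By endpoint:

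- **Incidence in young women:** negligible once 2004–2017 baseline incidence is in the model.
- **Endpoints analysed by difference-in-differences with a sound before value:** a main effect gains nothing. Stratum by period gained about 2–6% in the incidence simulation; the gain for men's outcomes cannot be derived from the article.
- **Men's home-test uptake and post-test linkage:** the most exposed, if the single year since home testing began supplies no usable before value. The excess in the standard error is at most about 3% at R² = 0.05 and about 15% at R² = 0.25, and less once within-cluster variance counts.

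The direction follows from the design. The sizes rest on the assumed k and R².

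**What to change.** State in the Statistical analysis section that the four-level incidence stratum enters the primary and secondary arm-comparison models:

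- as a fixed effect in single-period models, in particular test uptake and linkage if no before value is used;
- as a covariate or stratification factor in the Cox models;
- as stratum by period, not as a main effect alone, in the difference-in-differences models.

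Call it the incidence stratum, because the Study design section also uses the word strata for the four arms. Say as well which before value, if any, serves uptake and linkage.

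The cost is one or two sentences and three degrees of freedom with 45 clusters; in a cluster-level comparison of four arms, the residual falls from 45 − 4 = 41 to 38. For baseline-adjusted incidence the term is close to neutral, raising the standard error by about 1% in Step 3. The strata are already recorded, so no new data are needed.
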